#### Secondary outcome

The secondary outcomes include intracranial haemorrhage as defined by the SITS registry and functional outcomes at three months post stroke using the modified Rankin Scale (mRS) [55]. Intracranial haemorrhage events (parenchymal haematoma) will be identified from the TIPS database and will be monitored annually during the intervention and follow-up phases by the research team to ensure that it does not exceed international benchmarks [56]. Sites will be provided with additional support if benchmarks are exceeded. Monitoring of secondary outcomes will not interfere with established governance processes for reporting and monitoring of adverse events in the health system. Functional outcomes will be scored as good (mRS = 0 to 1) or poor (mRS = 2 to 6) by the treating clinician or stroke nurse. The mRS has demonstrated reliability and validity for use by clinicians and stroke nurses [57]. The percentage of tPA-treated stroke cases having a good outcome (mRS <2) at three months post stroke will also be monitored annually by clinical experts in the research team through the post-intervention NSF data collection.

### Process measures

Pen and paper staff surveys will be conducted at all participating hospitals regarding perceived barriers and facilitators to tPA implementation. Survey items include: perceptions of tPA efficacy, local policies about tPA, knowledge of tPA, skills relating to assessment for and administration of tPA, challenges in tPA implementation, training relating to tPA, expertise and confidence in relation to tPA, contingencies relating to tPA, participant’s gender, age, experience, staff role, and estimated rates of tPA administration. For intervention hospitals, engagement with each intervention activity will be assessed, including number and type of staff from each site attending each workshop or meeting. Assessment of baseline overall readiness for change will also be assessed by a member of the research team using a readiness for change checklist based on the work of Warrick *et al*. (2009), Kasurinen *et al.* (2002), and the National Institute for Health and Clinical Excellence (2007). The full version of the process measure tools can be obtained from the corresponding author.

### *Intervention* components and activities

The TIPS intervention components described below are grounded in behavioural theory and accord with the Behaviour Change Wheel (BCW) method [47]. The BCW emphasises the importance of ensuring that proponents have the capability, opportunity and motivation to perform the desired behaviour through interventions such as education, persuasion, incentivisation, coercion, training, restriction, environmental restructuring, modelling and enablement. A situational analysis based on the ‘patient journey’ is a foundational intervention component in that it delineates the steps and associated staff roles involved in successful delivery of thrombolysis. The TIPS intervention components are delivered via a number of intervention activities, the timing and content of which is presented in Figure 2.

**Figure 2 F2:**
[figure not shown]
Timing of delivery of intervention activities.

## Component 1. Situational analysis – clarifying the patient journey

Careful delineation of the phases of care was carried out by the research team on the basis of earlier work at a single site [40], beginning at the point of seeking emergency medical care (hospital or paramedic). The situational analysis follows the journey of a stroke patient including pre-hospital assessment, triage, clinical assessment, imaging, final clinical assessment, preparation and delivery of thrombolysis. The tasks and staff roles involved along the patient journey are described in Table 1. Examination of how well each of the steps and roles described in the situational analysis will be implemented at a particular site is embedded in a number of intervention activities, including a pre-workshop meeting between the primary change agent and the champions at each site, collaborative workshops involving a team from each site, and site-based working group meetings. In the context of each of these intervention activities, the situational analysis facilitates identification of barriers and facilitators to increasing the number of patients who are appropriately thrombolysed.

## Component 2. Change agents - educating, persuading and modelling

Much of the work on organisational change emphasises the importance of champions or leaders in order to increase the rate of adoption of a desired change [58,59]. In the context of TIPS, change agents will interact with participants to educate, persuade and model desired behaviours throughout the change process. TIPS change agents include primary change agents who liaise with each of the intervention sites and change agents or ‘champions’ located at each site. Stroke nurses from the research team will act as stroke nurse ‘champions’ to monitor and encourage completion of the nurse professional development training (see Component 5). Members of the research team ([name]) have been identified as the primary change agents, selected on the basis of meeting criteria for leadership and ability to enact education, persuasion and modelling at a national level [59]. The activities of the primary change agents involve identification of Site Champions and assisting the Site Champions with obtaining endorsement from senior hospital administrators or executives. During the intervention phase, the primary change agent will make regular contact (by email or telephone) to discuss any questions or concerns relating to recent cases of thrombolysis. The primary change agents will also lead education and training aspects of the communal workshops, and attend site workshops. The Site Champions will be the drivers of change at each site, engage with those involved in clinical work flow decisions, and will form a working group comprising key local staff from para-medicine, emergency, stroke care, and imaging. The Site Champions will lead the site working groups in setting goals, identifying actions, and reviewing performance designed to achieve change. The Site Champions are selected on the basis of clinical role (generally lead neurologist and lead stroke nurse).

## Component 3. Information-based target setting – persuasion and incentivisation

Target setting has been established as an important motivator and driver of change on an individual and system level [60]. Information-based target setting involves a process of setting overall targets for appropriate and achievable rates of thrombolysis for each site. Importantly, a series of interim targets or successive approximations will be set during the course of the intervention period.

During the pre-workshop meeting, the Site Champions at each intervention hospital will set a preliminary target for increased tPA administration at that hospital with the guidance of the primary change agent. This target will be reviewed at the first communal workshop in collaboration with members of the site-based working group. Targets are framed based on baseline thrombolysis rates and should be challenging but achievable to create a collective expectation of change and experience of achievement. Interim targets will also be set, based on perceived achievable changes in performance in successive three-month periods throughout the intervention phase.

## Component 4. Collaborative problem solving - education, modelling and enablement

Collaborative problem solving is central to commonly-used quality improvement strategies [61-63] and aims to harness the knowledge, skills and support of a group. Collaborative problem solving will occur within site working groups during their bi-weekly meetings. Bi-monthly teleconferences between the primary change agent and representatives from each of the intervention site-based working groups will explore experiences of all groups in relation to identifying barriers and implementing solutions. An evidence-based process will be used whereby groups attempt to analyse the problem before attempting to search for a viable solution [63].

## Component 5. Professional development – education, training and restriction

Detailed education and training regarding clinical decision making for thrombolysis will be provided via web-based educational modules with a strong emphasis on achieving accepted levels of competency in key skills such as decision making. Web-based approaches provide highly accessible, flexible and effective approaches to learning, particularly when an interactive case-based approach is used [64]. The TIPS website is available to intervention sites via a unique log-in for each participant.

For clinicians, the website contains didactic training modules with a test at the end of each module and a series of case studies where clinicians test their clinical judgement against a consensus-based logic frame for a set of stroke cases. In each case, the clinician is provided with feedback regarding the appropriateness of the decision and links to further reading if required. Clinicians are asked to continue with the case studies until they have achieved an agreed level of competence in decision making. Lead clinicians are asked to ensure that all relevant staff including emergency physicians and registrars complete the training prior to caring for potential stroke patients. The website provides information and training for paramedics in the identification of potential stroke patients. Both the clinician and paramedic training modules were developed by members of the TIPS research team and colleagues.

NET SMART-Junior, a distance-accessible competency-based learning system covering evidence-based management of acute stroke patients, will serve as the educational platform for standardised nursing education in the TIPS trial. The NET SMART system offers rolling entry/completion times supported by self-learning paced programming. NET SMART-Junior is accredited by the Arizona State University, College of Nursing and Healthcare Innovation (Tempe, Arizona, USA) to deliver continuing education credits internationally for completion of modular units consisting of pre-test/post-test and clinical skills measures. TIPS participants will be asked to complete a selected number of training modules and to discuss their results with their nurse ‘champion’.

The TIPS website also contains scientific literature relating to thrombolysis, and tools and resources such as those from the PAST trial [40]. In addition to training in decision making skills, training in the skills of being a champion will be provided. Change champion training will also occur as a component of the communal workshops in the form of group-based reflective activities, followed by self-directed tasks and opportunities for engaging with ongoing external training or self-directed learning.

## Component 6. Performance feedback - persuasion, modelling

Given the strategic importance of providing performance feedback in order to achieve clinical practice change [65,66], local and comparative feedback will be provided. Sites will be provided with their three-monthly estimated proportion of ischaemic stroke cases who receive thrombolysis, graphed against site targets. Comparative data will be provided, showing each site how it compares to other intervention hospitals in a de-identified format (*i.e*., other hospital names not disclosed), to create a positive level of competition among peers. This information will be made available to the participants via their unique logins on the TIPS website and also forwarded directly to Site Champions.

## Intervention sustainability

Achieving sustainability: Throughout the intervention period, there will be a focus on identifying and enacting strategies to embed changes in practice and ensure ongoing practice is monitored via mandatory recording and reporting of thrombolysis delivery. During every collaborative intervention activity (*e.g*., workshops, site-based meetings, inter-site teleconferences), sustainability will be discussed in order that a strong focus on sustainability is maintained. Strategies for achieving sustainability will include: i) key steps in the process of care (*e.g*., time from arrival to handover to stroke team and coverage of imaging services) as part of local standard recording and internal reporting; ii) establishing ongoing communities of practice/clinical networks or including thrombolysis as one of the priority initiatives of existing clinical networks; iii) establishing networks for ongoing mentoring, including formal mentoring relationships that link groups of staff across hospitals; iv) including numbers and proportions of thrombolysed patients in standard reporting to hospital executives and local health districts; v) incorporating the requirement for completion of the TIPS web-based training modules as part of orientation for medical staff in all relevant departments; and vi) establishment of the web-based training as a locally-recognised professional credential required for those involved in the care of stroke patients in the local health district. Site-based working groups will also be encouraged to identify and enact other locally-relevant strategies for achieving sustainability.

Measuring sustainability: Progress in achieving the above sustainability strategies will be monitored during both the intervention and follow-up phases via bi-monthly site teleconferences and post-test staff surveys as part of the study process measures. The degree to which each of the intervention activities (regular site working group meetings, completion of training modules by new staff, entry and monitoring of the number of thrombolysis cases) continues to occur during the follow-up period (Year 4) will also be monitored as part of the study process measures.

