##### *Stratified* randomisation

Hospitals will be stratified according to their stroke thrombolysis rates at baseline: very low (0% to ≤4.00%), low (>4.00% to ≤10.00%) or moderate (>10.00%). Baseline thrombolysis rate was considered important for the following reasons: A ‘very low’ thrombolysis rate suggests some impediments to thrombolysis, potentially limiting the ability of the site to respond quickly to the intervention. Sites categorised as having a ‘low’ thrombolysis rate may have the greatest potential for achieving change during the study, due to having substantial room for improvement. Conversely, a site with a ‘moderate’ baseline rate of thrombolysis may have limited opportunity to demonstrate further substantial improvement on the outcome measure.

Hospitals will be randomised at one time (effectively achieving allocation concealment) to either the intervention arm or the control arm with a 1:1 allocation ratio, using a computer generated stratified randomisation scheme in StatsDirect. Intervention hospital staff will not be effectively blinded to their allocation, in that they will be aware of their own involvement in intervention activities. There will be minimal interaction with control hospitals during the intervention phase.

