### Procedure

#### Site recruitment

Eligible hospitals were identified from National Stroke Foundation (NSF) audit records and state-based clinical SCU networks. Clinical leaders in stroke at each potentially eligible hospital have been contacted by a clinical leader from the research team to verify eligibility and have been invited in person or by telephone to provide in-principle support to participate in the study following discussions with relevant decision makers at each site. A signed memorandum of understanding or equivalent consent agreement between each hospital and the research team has documented agreement by all relevant parties to collaborate for the whole period of the study. Ethical approval for the study has been obtained from relevant human research ethics committees in each state, from each participating hospital and from The University of Newcastle Human Research Ethics Committee.

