## Sample size

From baseline data, it is estimated that participating hospitals will have an average of approximately 150 stroke patients per year, that 5% of stroke patients in the control group will be prescribed tPA, and that the average co-efficient of variation across strata will be approximately 0.4. With 10 hospitals per group, the study will have 80% power with a 5% significance level to detect an absolute difference of 7% to 10% [67]. The subgroup analysis of hospitals with baseline tPA rate of <10% will also have similar power to detect this difference, as, although the number of hospitals per group will be smaller, the baseline tPA rate will also be lower.

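### The sustainability strategies can carry part of the TIPS intervention to control hospitals before or during the Year 4 outcome, because the district credential, network and mentoring steps are not limited to intervention hospitals

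*Protocol article*

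**What the plan says.** All references are to the protocol article.

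- *Intervention sustainability* has sites identify and enact embedding strategies throughout the intervention period, with progress monitored in both the intervention and follow-up phases. Strategy (vi) turns the TIPS web training into a "locally-recognised professional credential required for those involved in the care of stroke patients in the local health district". Strategy (iii) sets up mentoring networks, including "formal mentoring relationships that link groups of staff across hospitals". Strategy (ii) offers a choice: new communities of practice or networks, or making thrombolysis a priority of networks that already exist.
- *Methods and design* puts the intervention in Year 3 and follow-up in Year 4. It says that control hospitals get no intervention and may change practice on their own initiative. *Aims* defines the primary outcome at follow-up.
- *Component 5*: "The TIPS website is available to intervention sites via a unique log-in for each participant".
- *Stratified randomisation* names baseline thrombolysis rate as the only stratification factor and adds: "There will be minimal interaction with control hospitals during the intervention phase".
- *Site recruitment*: "Eligible hospitals were identified from National Stroke Foundation (NSF) audit records and state-based clinical SCU networks".
- *Engagement of paramedic/ambulance service* is the only place where spread between arms is acknowledged, and it concerns ambulance officers alone. *External factors* deals with outside policies and reforms, not with spread of the intervention itself.

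**The concern.** The trial compares the intervention with usual care. A training requirement that applies to a whole district covers any control hospital in that district, and it uses material that *Component 5* reserves for intervention sites. The three statements (no intervention for controls, website for intervention sites, credential across the district) cannot all hold wherever the arms share a district.

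The timing makes this matter. Strategies enacted in Year 3 and carried into Year 4 come before or overlap the period in which the primary outcome is measured, and the minimal-contact statement is worded for the intervention phase only. If the intervention raises thrombolysis rates, any part of it that reaches controls raises their rates too and shrinks the observed difference. The *Sample size* section makes no allowance for this. Unlike the ambulance route, which the protocol says cannot be controlled, this route is created by the protocol's own wording and can be closed by it.

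**Working it through.** **1. Can the arms overlap?** Nothing in the randomisation keeps districts or networks in one arm. Under simple 10:10 allocation of 20 hospitals, two hospitals in the same district fall in opposite arms with probability 10/19 = 53%. This says what would happen if a district holds two trial hospitals. The documents do not say whether any does.

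**2. The plan's own power figure.** The inputs from *Sample size* are:
- "With 10 hospitals per group" (c = 10);
- "participating hospitals will have an average of approximately 150 stroke patients per year" (m = 150);
- control rate p0 = 5%;
- coefficient of variation k = 0.4.

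The section states that "the study will have 80% power with a 5% significance level to detect an absolute difference of 7% to 10" per cent. I take the test as two-sided. The standard formula for cluster-level proportions (Hayes and Bennett), with a = 1 for an unmatched design, gives

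V = p0(1 − p0)/m + p1(1 − p1)/m + k²(p0² + p1²)

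power = Φ( √[(c − a)(p1 − p0)²/V] − 1.96 ).

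On these inputs the difference detectable with 80% power is about 5.1 points (5.5 with a = 2), so the stated 7 to 10 is not reproduced and errs on the cautious side. That mismatch is a separate matter. Here it means power has to be shown both ways.

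- True difference 7 points (5% v 12%): V = 0.000317 + 0.000704 + 0.002704 = 0.003725; √(9 × 0.0049/0.003725) = 3.44; power = Φ(1.48) = 93%.
- True difference 10 points (5% v 15%): V = 0.000317 + 0.000850 + 0.004000 = 0.005167; √(9 × 0.01/0.005167) = 4.17; power = Φ(2.21) = 99%.

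**3. Illustration of dilution (assumed, not from the documents).** Let x of the 10 controls gain a fraction f of the effect d. The control rate becomes 5% + d·f·x/10, and the observed difference becomes d(1 − f·x/10).

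For x = 5, f = 0.5:
- d = 7: observed 7 × 0.75 = 5.25 points (6.75% v 12%). V = 0.000420 + 0.000704 + 0.003033 = 0.004157; √(9 × 0.002756/0.004157) = 2.44; power = Φ(0.48) = 69%.
- d = 10: observed 7.5 points (7.5% v 15%). V = 0.000463 + 0.000850 + 0.004500 = 0.005813; √(9 × 0.005625/0.005813) = 2.95; power = Φ(0.99) = 84%.
- d = 7, with the stated 80% taken at face value: the standardised effect is 1.96 + 0.84 = 2.80, so power = Φ(2.80 × 0.75 − 1.96) = Φ(0.14) = 56%.

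Range of assumptions, from the protocol's inputs with a = 1:

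| Controls exposed | Share of effect gained | Observed, true 7 | Power | Observed, true 10 | Power |
|---|---|---|---|---|---|
| 0 of 10 | none | 7.0 | 93% | 10.0 | 99% |
| 1 of 10 | half | 6.65 | 90% | 9.5 | 98% |
| 3 of 10 | half | 5.95 | 81% | 8.5 | 93% |
| 5 of 10 | half | 5.25 | 69% | 7.5 | 84% |
| 3 of 10 | all | 4.9 | 62% | 7.0 | 78% |

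These figures leave out the extra spread that partial exposure would create among control hospitals, so they are slightly generous.

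**The case against.** A reader might infer that the plan pushes training, mentoring and networks out to whole districts, and that control hospitals will therefore receive the intervention. The documents do not support that. No section shows a control hospital sharing a district with an intervention hospital. Strategy (ii) is an either/or. Strategy (iii) can be read as mentoring among intervention hospitals, in line with *Component 4*, where the teleconferences join intervention working groups. Only (vi) is district-wide on its face. Progress is monitored through both phases, so the text does not imply that every strategy is in place before Year 4.

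There are also safeguards. The no-intervention rule for controls carries no time limit, and the log-in restriction would, as written, keep control staff out of the modules. These reduce the risk, but they contradict (vi) rather than qualify it, and the protocol does not say which prevails.

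A second tempting inference is that a null result could not be told apart from diffusion. That goes too far: the staff survey is repeated at follow-up, runs at all participating hospitals and asks about local tPA policies and training (*Data collection*, *Process measures*). Two baseline years would also help to show a rise in control rates. This gives some evidence on diffusion, though it cannot restore a lost contrast.

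Third, the leakage fractions are arbitrary and may be high. Site champions, targets, working groups and performance feedback stay at intervention hospitals. The 24-hospital US cluster trial described in the *Background* ended at 2.79% v 2.10%, a gap of 0.69 points, from a multi-part programme, which makes a 3.5-point gain from partial exposure look large. This stands: the scenarios show sensitivity and are not forecasts.

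Finally, embedding change is part of what is being tested, so deferring these steps has some cost to the intervention. That is fair, but embedding within intervention hospitals does not need to reach control hospitals.

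**Conclusion.** The point holds as a gap in the protocol that can be avoided, not as a demonstrated contamination. Strategy (vi) is district-wide and conflicts with *Methods and design* and *Component 5*. Strategies (ii) and (iii) are unrestricted rather than expressly district-wide. Nothing in the randomisation separates arms by district or network, the contact limit is not stated for the outcome year, and the limitations omit this route.

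The direction of any bias is towards zero, provided that the intervention works. The size is unknown, because it depends on shared districts or networks and on how much of the effect would carry over, and the documents give neither. In the illustration (half of the controls gaining half of the effect), power ranges from 56% to 84% according to the true difference and whether the stated power or the stated inputs are used. With lighter leakage it stays at or above 80% on the protocol's inputs. The illustration therefore does not show that the trial would be underpowered. The case for acting is that the change is cheap and protects the primary contrast.

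**What to change.** - Reconcile *Methods and design*, *Component 5* and *Intervention sustainability*: until Year 4 data collection closes, limit the credential in (vi), and any network or mentoring activity under (ii) and (iii), to staff of intervention hospitals. Defer district-wide and network-wide roll-out until then.
- In *Stratified randomisation*, extend the minimal-interaction statement to cover the follow-up phase as well as the intervention phase.
- Add this route to the limitations, beside the ambulance service.

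The cost is a change of protocol wording and a delay of about a year in wider roll-out. Hospital-level strategies, such as local recording of care steps, orientation training and reporting to hospital executives, are unaffected.
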